### Statistical analysis

No interim analysis is planned. Statistical analyses will be carried out after all outcome data has been collected. Feasibility objectives and acceptability of intervention outcome measures will be assessed using descriptive analysis, focusing on confidence interval estimation, rather than formal hypothesis testing. To assess the suitability of the intervention outcome measures for use with multilingual families, we will compare quality and responsiveness of the measures in families who do and do not speak English as their primary language.

### Qualitative analysis

Qualitative data from interviews will be transcribed and checked for accuracy against the original audio recordings. Anonymised transcripts will be analysed using the Nvivo data management programme (NVivo qualitative data analysis software; QSR International Pty Ltd) and analysed following a two-stage approach. In stage 1, transcripts will be coded to the domains of the TDF to extract the barriers and facilitators of implementing the trial from the perspective of service providers and families, followed by an inductive analysis of the themes within each domain. We will also explore any patterning of themes by individuals’ ethnicity, socioeconomic circumstances, and English language ability. Transcripts will be coded systematically and iteratively until saturation is achieved. Ten percent of transcripts will be coded by a second researcher to ensure reliability of the coding framework.

### Progression criteria

Progression to definitive trial will be informed by the results of three main progression criteria, based on Avery et al. [27]. A traffic light system will be used with red as an indication not to progress to trial and green indicating progression to trial. Amber indicates potential progress to trial with careful consideration of why these criteria did not reach green.
Recruitment—we anticipate a minimum of 60% of families identified and offered the intervention will be eligible to participate in the trial, and a minimum of 50% of these eligible families will consent to participate in the trial. These numbers will be assessed cumulatively over the course of the recruitment phase. Progression criteria are as follows:
Eligibility—60% and above = green, 50–60% = amber, and below 50% = redConsent—50% and above = green, 40–50% = amber, and below 40% = redProtocol adherence—families will be administered the quantitative assessment measures at specific time points, ensuring that assessments of the waiting control group align with those of the intervention group. Feasibility of running a trial using this design is dependent on the ability to adhere to the following timeline: pre-test within 1 month of Universal Language Screener, post-test 6 to 10 weeks following pre-test, and follow up at 5.5 months to 6.5 months after pre-test. Progression decisions will therefore be based on percentage adherence rates, i.e. 80% = green, 60–80% = amber, and less than 60% = red.Attrition rates—based on previous reported attrition rates for Talking Together, we have calculated a predicted attrition rate over the course of the trial. Progression decisions will be based on the proportion of the recruited sample that attends the 6-month follow-up, i.e. 80% = green, 70% = amber, and below 70% = red.

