### Design

This will be a two-arm randomised controlled feasibility study, with an experimental group and a waiting control group. Families will be randomised following baseline data collection collected at the standard universal screening assessment delivered in the home. The families allocated to the experimental group will receive the Talking Together programme within approximately 2 weeks of allocation, while the families allocated to the waiting control group will receive the programme after a 6-month waiting period. While the average waiting time in standard practice varies depending on a number of factors, with the majority of families seen within 3 to 4 months, many families wait up to 6 months for intervention. In order that we can ensure time of data collection is comparable across the intervention and waiting control groups, we have time-locked the assessments at 2 and 6 months following pre-test thereby mirroring but not exceeding the maximum wait time. Families will be fully informed of the timeline of the project at recruitment, it will be made clear that families do not have to participate in oTTer to receive Talking Together, and full information regarding withdrawal procedures will be provided.

Feasibility and implementation outcomes will be measured using child language assessments, measures of home learning environment and parent-child relationship, and monitoring data in the form of, for example, referral rates, waiting times, attrition rates, and completion rates.

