### Recruitment and randomisation

#### Sample size

Based on existing recruitment data, over the 9-month period of recruitment, we would expect BHT Education and Training to screen approximately 670 families and refer approximately 250 families to the Talking Together programme, although not all of these families will be eligible for the trial or consent to take part. Recommendations for feasibility studies suggest that at least 30 participants per group will allow sufficient precision when estimating study summary measures [20, 21]. As such, our minimum required sample size is 60 families. However, we have set a desired sample size of 120 families, which is in excess of the recommended 60 participants for a feasibility study [14, 15], to allow for attrition and provide more confidence that a future definitive trial can be successfully conducted (see Fig. 1) [14]. Currently, all families within Better Start Bradford with children of 2 years of age are offered a language screening home visit. For the purposes of recruitment, the LDWs will provide families with an information sheet and consent form to take part in the trial at the end of these language screening visits if the family is going to be referred to Talking Together and meets the oTTer eligibility criteria. Families who consent to take part in the trial will then be randomly allocated to the intervention group or the waiting control group (see Fig. 2).

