**Fig. 2 Fig2:**
[figure not shown]
Procedure for recruitment and consent in the oTTer feasibility study

Randomisation (1:1) will be carried out by a member of the data management (DM) team within BiB. Statistical software package STATA (‘ralloc’ command) will be used to generate a random list stratified by (a) whether the family was within a specific Children’s Centre reach area, (b) language of delivery (English or not), and (c) whether two or more children will be present during delivery of the intervention, using a block size of eight. Referrals from the LDWs with informed consent to take part in the trial will be entered onto SystmOne, a secure healthcare system managed by BTHFT. Once a week, the DM team will carry out randomisation and enter the allocation details onto SystmOne. The deputy language development programmes manager will then access the randomisation details and allocate families to the research assistants and LDWs as appropriate so that a schedule of assessment and intervention can be devised. It is not possible to fully blind the LDWs, RAs, and post-doctoral research assistant (PDRA). The LDWs and RAs will carry out the assessments with the intervention and control group respectively and therefore cannot be blinded to group membership. The PDRA will only have access to anonymised data, but will know the group allocation of all anonymous participants for the purposes of monitoring trial procedures and data analyses.

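### The retention light uses only the pooled proportion, so it can read green with one arm below the red line; separately, the timing-adherence percentage has no stated denominator

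*Protocol article*

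**What the plan says.** Under Progression criteria, the protocol article bases the attrition light on the whole recruited sample: "Progression decisions will be based on the proportion of the recruited sample that attends the 6-month follow-up, i.e. 80% = green, 70% = amber", and red below 70%. The criterion has no by-arm component.

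The protocol-adherence light in the same section concerns three windows: pre-test relative to the screener, post-test relative to pre-test, and follow-up relative to pre-test. Its stated purpose is "ensuring that assessments of the waiting control group align with those of the intervention group". The rule is "Progression decisions will therefore be based on percentage adherence rates, i.e. 80% = green, 60–80% = amber, and less than 60% = red". It does not say whether the percentage counts assessments or families, or whether the arms are combined.

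The Sample size section gives two planning figures: "we have set a desired sample size of 120 families" and "our minimum required sample size is 60 families". Allocation is 1:1. The Progression criteria mention a predicted attrition rate but give no value for it.

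**The concern.** A waiting-list design can lose families unequally. Controls are held for 6 months, whereas under standard practice the waiting time varies, "with the majority of families seen within 3 to 4 months". Intervention families finish the programme well before the 6-month visit. Pre-test and post-test are also done by different staff in the two arms (Data collection).

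Whether the control arm stays in the study is therefore one of the main things this feasibility study can tell the designers of the definitive trial. Loss that differs by arm would threaten the comparison in that trial, and a pooled percentage can look satisfactory while one arm does badly.

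The adherence criterion raises a different problem. If the percentage can be computed in more than one way, the same data can point to progression or against it, and the choice would be made after the data are seen.

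**Working it through.** **Inputs from the protocol.** Minimum 60 families, from the view that "at least 30 participants per group will allow sufficient precision when estimating study summary measures": 2 × 30 = 60, which reproduces. Target 120, so 60 per arm at 1:1. Retention: green at 80%, red below 70%. Adherence: green at 80%, red below 60%. True arm-specific rates are not given, so those used below are assumptions.

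**1. Can pooled retention be green with one arm red?** With equal arms, pooled retention is (a + b)/2. If it is at least 0.80 and b is at most 1, then a is at least 0.60. An arm between 60% and 70% is therefore red but compatible with a pooled green.
- 60 per arm: 41/60 = 68.3% and 55/60 = 91.7%; (41 + 55)/120 = 96/120 = 80.0%. The gap is 14/60 = 23.3 points, the smallest that produces the effect.
- 30 per arm: 20/30 = 66.7% and 28/30 = 93.3%; 48/60 = 80.0%. The smallest gap is 8/30 = 26.7 points.
- Extreme case at 60 per arm: 36/60 = 60% and 60/60 = 100%, again 96/120.

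**2. How often would it happen?** Retained counts are taken as independent binomials, one per arm. The joint probability is summed over all pairs with a pooled rate of at least 80% and at least one arm below 70%.

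| Assumed true retention | Pooled green, 60 per arm | Green with a red arm, 60 per arm | Green with a red arm, 30 per arm |
|---|---|---|---|
| 80% / 80% | 55% | under 0.1% | 0.3% |
| 85% / 75% | 55% | 0.7% | 1.7% |
| 90% / 70% | 55% | 8.6% | 8.2% |
| 92% / 68% | 56% | 16.2% | 13.2% |
| 95% / 65% | 56% | 30.7% | 23.0% |

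The chance of pooled green hardly moves down the table, because every row averages 80%. The pooled light therefore carries almost no information about the difference between arms.

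**3. Does the same masking apply to adherence?** The text does not say that adherence is pooled. If it were, the inequality in step 1 gives a lowest possible arm rate of 60% with equal arms, and red is below 60%. Enumeration finds no such pair at 60/60 or at 30/30. It appears only with unequal arms and near-perfect adherence in the larger one, for example 61/61 and 35/59 = 59.3%, giving 96/120.

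**4. What does the missing adherence denominator do?** Suppose every window is met by 80% of families and all families have all three assessments.
- Per assessment: (0.8 + 0.8 + 0.8)/3 = 80%, green.
- Per family, all three windows met, windows independent: 0.8³ = 0.512, red.
- Per family without assuming independence: from 1 − 3 × 0.2 = 40% (red) up to 80% (green, if the same families miss every window).

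**5. Band wording.** Retention gives colours at 80%, at 70% and below 70%, and none in words between 70% and 80% or above 80%. In the adherence rule, exactly 80% belongs to both green and amber. The eligibility and consent bands in the same section do spell out an open-ended top category.

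**The case against.** The best defence has four parts.

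- **The criteria inform the decision; they do not mechanically make it.** The protocol also records the number, timing and reasons of withdrawals and the proportion with data at each time point, and it interviews families from both arms. A by-arm table may sit in an analysis plan not shown. This stands as a limit on the harm: the team could notice an imbalance. But the colour rule is fixed in this document and takes no account of it.
- **Masking needs a large gap.** This stands. At 85% and 75% the event has probability 0.7% at 60 per arm, and no figure in the protocol shows that a gap of 23 points is likely. The Comparator and Design sections also say that the control wait does not exceed the current maximum and that many families already wait that long, which weakens any presumption of heavy control loss.
- **A by-arm rule costs power to progress.** This depends on the rule. If green required at least 80% in each arm, a true 85% in both arms would see the chance of green fall from 0.95 to 0.80 at 60 per arm. Withholding green only when an arm is red costs far less: under 0.1% at 60 per arm and 0.2% at 30 per arm, for the same true rates.
- **The band gaps have an obvious intent.** This stands; they are wording points and do not cause the masking.

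A reader might also infer that the adherence light can be green while one arm is red. The document does not support this. Pooling is not stated for adherence, and step 3 shows that with equal arms it could not happen. A pooled figure could at most hide an amber arm.

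**Conclusion.** The point holds for retention. By its wording the light rests on one pooled proportion, and at both of the protocol's own sample sizes it can be green with an arm below 70%. The size is moderate and conditional. It takes a gap of about 23 points at 60 per arm, and has a probability of about 16% if true retention is 92% and 68%, rising to about 31% at 95% and 65%. It is negligible when the arms are alike. These rates are assumed and the calculation treats families as independent.

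A reader might take the 55% to 56% chance of pooled green as the size of the problem. It is not: that chance is the same with no arm difference, because it reflects an average lying on the threshold.

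Separately, the adherence criterion is under-defined. Identical data can be green per assessment and red per family, at about 51% under independence. It also requires no by-arm figure, although alignment between arms is its stated purpose. The band wording is minor. The rules should be changed before the progression decision is taken; nothing here invalidates the study.

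**What to change.** 1. **Retention.** Calculate 6-month retention by arm as well as pooled. Do not call the criterion green if either arm is in the red band: the light is then amber at best, and the difference between arms is considered explicitly.
2. **Adherence.** Define it as the share of assessed families who were in window, with one figure for each of the three windows, shown by arm. Restricting it to assessed families keeps attrition from being counted twice.
3. **Bands.** Write retention as 80% or more green, 70% to below 80% amber, below 70% red. Assign exactly 80% adherence to one band.

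The data are already being collected, so the cost is wording and one table. The downside is smaller denominators by arm and a somewhat stricter retention rule. With 41/60 observed, the Wilson 95% interval is 55.8% to 78.7%, against 72.0% to 86.2% for 96/120, so by-arm colours should be read with their intervals.

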### Data monitoring and confidentiality

#### Quantitative outcome data and monitoring data

BHT Early Education and Training, BiB, and Better Start Bradford have a data sharing agreement. Where participants have consented to data sharing, data will be transferred to BiB automatically through the SystmOne database, i.e. SDQ, MORS, home learning environment, CDI, and WellComm, as well as recruitment and monitoring data. A data sharing agreement is also in place between BiB and the University of York, allowing BiB as data controller to share anonymised data with the PI and research team as data processors. Data quality will be monitored as a standing item on the monthly oTTer meeting agenda.

#### Qualitative data

RAs will upload audio recordings of interviews to password protected NHS laptops. Once uploaded, the recordings will be held in BiB on a secure computer server and deleted from the laptop and audio recording equipment. Transcripts will be anonymised before analysis and stored on a central secure computer at BiB. Only anonymised scripts will be shared with the research team for analysis and recordings will be destroyed after transcription.

### Project oversight

The programme management team is made up of the principal investigator, co-investigators, PDRA, data manager, and research assistants. The team will meet monthly to monitor the progress of the project, discuss challenges, set priorities, and talk about next steps.

The proposed project sits within the existing work of Better Start Bradford and BiB, and will therefore come under the purview of an established structure of expert and stakeholder advisory groups [11]. As such (and given the low risk nature of the research), a separate Data Monitoring and Ethics Committee is not required. This network of existing groups will enable the research team to ensure that the project is embedded in the wider context of Better Start Bradford and BiB.

In addition, a bespoke advisory group will be convened with oversight for this specific project. This group will be made up of members from the existing advisory groups related to the wider work of BiB and Better Start Bradford’s language and communication work, and parent representatives from the community. This group will meet with the research team biannually over the course of the project and advise on key methodological decisions, outputs, and dissemination. Meetings will be held in Bradford to ensure community members are able to attend. We will also seek advice from relevant members of the advisory board outside of these meetings as appropriate.

### Publication policy

The study falls under the rubric of the Better Start Bradford Innovation Hub and will therefore use the Better Start Bradford Innovation Hub publication policy that follows the BMJ rules on authorship and contributorship to guide decisions around publications (https://www.bmj.com/about-bmj/resources-authors/article-submission/authorship-contributorship). The publication policy is held at BiB and has been agreed by all BiB collaborators working on the Better Start Bradford programmes.

### Trial status

The trial is open and has been recruiting since October 2018. The trial was registered with ISRCTN in February 2019.

## Discussion

Recent reports have raised awareness of the need for increased early support for children with speech, language, and communication needs [1, 4]. Oral language difficulties have been linked with poor educational, employment, and mental health outcomes [4]. Research suggests that a strong foundation in language is fundamental to later language skills, and a corollary of this is that a communication-rich home language environment is key. However, the evidence for programmes that support parents in providing this strong foundation is lacking [6]. This programme of work is the first step towards developing a definitive randomised controlled trial to evaluate the effectiveness of one such programme: Talking Together. Designed and delivered by BHT Early Education and Training, the programme is one of a suite of services provided as part of the Better Start Bradford project and aims to improve children’s language outcomes through improving parent-child interactions. This study aims to inform the feasibility of delivery of a future definitive trial and as such will not provide evidence of effectiveness. However, it will provide invaluable information regarding the feasibility of using random allocation without adversely impacting on service delivery. It will identify the most effective measures to be used as primary and secondary outcomes (and how they can be administered), and through the qualitative work with service providers, it will identify any issues of implementation both for the service as a whole and for the service as part of the trial. Our qualitative work with families will help to identify barriers and facilitators to engaging with the Talking Together programme from an ethnically and socioeconomically diverse community. This increased understanding will lead to more informed commissioning decisions and service provision within Bradford and elsewhere, as well as providing the foundation for a large-scale RCT of the Talking Together programme.

## Data Availability

Study materials are available through the oTTer website: https://otterproject.wixsite.com/otter. Data from the feasibility trial will be available after final evaluation and publications of the study and can be requested following procedures described on the Born in Bradford website: www.borninbradford.nhs.uk.
